## Abstract

**Background:**

A number of children experience difficulties with social communication and this has long-term deleterious effects on their mental health, social development and education. The proposal presented in this article describes a feasibility study for a trial to test an intervention (‘E-PLAYS’) aimed at supporting children with social communication impairments. E-PLAYS harnesses technology in the form of a novel computer game in order to develop collaborative and communication skills. Preliminary studies by the authors show that when E-PLAYS was administered by the research team, children with social communication impairments showed improvements on communication test scores and on observed collaborative behaviours. The study described here is a pragmatic trial to test the application of E-PLAYS delivered by NHS speech and language therapists together with schools.

**Methods:**

This protocol outlines a two-arm feasibility cluster-randomised controlled trial of the E-PLAYS intervention with treatment as usual control arm, with randomisation at the level of the speech and language therapist. The aim of this study is to ascertain whether it will be feasible to progress to running a full-scale definitive trial to test the effectiveness of E-PLAYS in an NHS setting. Data relating to recruitment and retention, the appropriateness of outcomes and the acceptability of E-PLAYS to participants will be collected.

Speech and language therapists will select suitable children (ages 4–7 years old) from their caseloads and deliver either the E-PLAYS intervention (experimental group) or treatment as usual (control group). Assessments will include blinded language measures and observations, non-blinded teacher-reported measures of peer relations and classroom behaviour and parent-reported use of resources and quality of life. There will also be a qualitative process evaluation.

**Discussion:**

The findings of this study will inform the decision as to whether to progress to a full-scale definitive randomised controlled trial to test the effectiveness of E-PLAYS when delivered by speech and language therapists and teaching assistants within schools. The use of technology in game form is a novel approach in an area where there are currently few available interventions.

**Trial registration:**

ISRCTN 14818949 (retrospectively registered).

## Background

Children with social communication impairments experience difficulties with using linguistic context to understand speakers’ meanings and, more broadly, with applying conventional norms and expectations from the wider society to relate to others [1]. To illustrate, children with social communication impairments are likely to find it difficult to take turns during conversation, maintain a topic of conversation appropriately, recount coherent narratives, respond contingently, make inferences, understand non-literal language such as jokes, irony or sarcasm, repair communication breakdowns and generally follow conversational conventions. Pragmatic language skill may be defined as selection of the appropriate message or interpretation in relation to the communicative context [2]. The terms ‘social communication’ and ‘pragmatic language’ are commonly used to refer to similar skills.

Recent systematic reviews of interventions for ‘social communication impairments’ or ‘pragmatic language impairments’ [3, 4] have adopted broad definitions for these terms encompassing both verbal and nonverbal aspects of communication to include abilities such as facial expression recognition and production [5]. Whilst the terms ‘social communication’ and ‘pragmatic skill’ have often been used interchangeably in the research literature [1], for the current proposal, we follow the suggestion by Matthew et al. [6] and define ‘pragmatics’ more specifically as the *linguistic* component (excluding facial communication and other non-verbal communication) of social communication.

Children with social communication impairments are a heterogeneous group and encompass both clinical and non-clinical groups. Clinical groups include the categories of ‘Language Impairment’ (also commonly known as ‘Specific Language Impairment’ and, more recently, ‘Developmental Language Disorder’), ‘Social (Pragmatic) Communication Disorder’ and ‘Autism Spectrum Disorders’ as defined in the Diagnostic and Statistical Manual of Mental Disorders (DSM-V; [7]). ICD 10 [8] as well as listing a number of pervasive developmental disorders (autism, Asperger’s and other pervasive developmental disorders) also describes a number of developmental disorders of language. Children experiencing difficulties with social communication are not limited to those covered by these DSM-V and ICD 10 diagnoses, however. Social communication and pragmatic language difficulties have also been shown to be associated with other clinical populations, notably those with ADHD [9] or conduct disorder [10, 11] and non-clinical groups such as shy children [12, 13]. There are also indications that social communication disorders are severely under-diagnosed, particularly in children of low socio-economic status [10, 14].

Research concerning children identified as having pragmatic language difficulties demonstrates that effects are far-reaching. Recent studies have shown associations between pragmatic language difficulties and behavioural problems [15], especially of the disruptive, externalising kind. Healthcare costs (excluding education costs) have been shown to be 36% higher for 4-year-old children with language disorders than for typically developing children [16]. A number of studies have shown long-term negative effects: children with social communication impairments experience problematic peer relationships [17] and are commonly rejected and victimised by peers at school [18, 19]. Individuals diagnosed with pragmatic language impairments as children were found to experience continuing problems with establishing social relationships (such as friendships) later in adulthood [20].

A particularly important skill for successful adult functioning, to which social communication is central, is the ability to collaborate with others. Collaborative and team-building skills are recognised as vital to future adult employment and participation in society [21]. A number of collaborative activities between children (such as collaborative learning, cooperative learning or peer tutoring) now commonly take place in classrooms and have generally been judged to be beneficial in terms of improved learning (e.g., [22, 23, 24]). Collaborative working has also been shown to improve peer relations and facilitate children’s feelings of belonging [25, 26]. However, group and dyadic work is not invariably beneficial, only collaborations where children are actively engaged and that are characterised by high-quality questioning, explanation, clarification of ideas, discussion and generally positive affect have been found to be productive [21].

Given their difficulties, it is to be expected that children with social communication impairments will struggle with collaborative group working and recent studies do indeed bear this out. By comparison to typically developing children in collaborative contexts, they can be aggressive or withdrawn [27], show more irrelevant behaviours and share less [28], ignore others’ questions and requests and give poorer directions [29].

Interventions to support pragmatic language and collaborative working are limited. The use of technology and gaming has been highlighted as a positive tool for facilitating communication and collaboration with peers in children with communication difficulties (e.g. [30, 31]). The application of computer technology for collaborative games to support children’s communication has a number of unique advantages over non-technological approaches. Children with social communication impairments are frequently overwhelmed by the complexity and unpredictability of social interaction. Computer games designed for two or more children to play together can be formatted so that they provide a ‘scaffold’ that guides and structures the interaction between children (for a review, see [32]). Properly designed, use of a computer game can support communication by structuring collaboration between children so that they solve problems within a fun environment together in partnership [33–35]. Typically, in collaborative activities, children with social communication disorders either participate very little, lacking the confidence to become involved or, alternatively, may attempt to dominate and run the activity solely according to their own agenda [27]. Managing these behaviours presents a serious challenge for speech and language therapists, teachers and teaching assistants [36]. Technology can be used to regulate turn-taking, ensuring equal participation between all players and preventing exclusion of any children. Furthermore, rule enforcement and reward-giving (such as virtual ‘prizes’) by a computer, rather than an adult, is viewed by children as more consistent, fairer and less arbitrary [37]. The flexibility afforded can also be harnessed to sustain children’s interest and concentration by adding surprises, colourful animations and unusual sounds and keeping the game flowing at a suitable pace [31, 38].

We have developed and carried out initial testing for a computer game intervention which aims to improve pragmatic language skill and the ability to collaborate in children with social communication impairments. Preliminary efficacy testing for ‘E-PLAYS’ (formerly known as the ‘Maze Game’) is described in Murphy et al. [29, 39] on 32 children randomised either to the intervention or to usual school practice. Children who received the computer game intervention showed significant increases on communication test scores, in the use of high-quality questioning and listening skills and in their positive ratings about collaborative work with peers [39]. It is important to note that for these studies, the intervention was delivered to the children by a trained, post-graduate psychology research assistant who was supervised by the research team. This represents an ‘ideal’ scenario for intervention and it is likely that results would differ from implementation in ‘real-life’ by professionals who would not have the benefit of intensive supervision, time and training. Successful implementation by the National Health Service (NHS) speech and language teams throughout the UK would require the E-PLAYS intervention to translate to a setting in which speech and language therapists and teaching assistants could learn to use it together without research team input or supervision.

Following on from our preliminary work with E-PLAYS [29, 39] therefore, the aim of the present study is to establish the feasibility of running a full-scale clinical trial to evaluate its clinical- and cost-effectiveness when implemented within the National Health Service (NHS) in the UK. Speech and language therapists are employed by and work within the NHS, but their day to day work frequently takes place in the school setting, rather than in clinics, particularly for young children.

This feasibility study will explore potential challenges and aim to develop a protocol for a follow-on large-scale RCT. Specific objectives include testing the *recruitment procedure* and recording the number of participants recruited over time. An important aspect will focus on determining *treatment fidelity*; E-PLAYS will be delivered by teaching assistants who have been trained by NHS speech and language therapists. We will also aim to establish the *acceptability* of E-PLAYS with speech and language therapists and with teachers, teaching assistants, parents and children and also explore the acceptability of randomisation to a control group. We will also seek to determine the feasibility of collecting resource-use data and quality of life measures for the purpose of calculating relative *cost*-*effectiveness*.

## Method

### Design

The design is a two-arm feasibility cluster-randomised controlled trial (cRCT) with randomisation at the level of the speech and language therapist (SLT). Each participating child receiving the E-PLAYS intervention will be a child with social communication impairments. For each participating child, there will be an associated teacher and parent who will complete questionnaires, a speech and language therapist and teaching assistant who will deliver the intervention and a typically developing child from the same class who will partner the child to play the E-PLAYS game. For ease of reference, these will be called ‘participant groups’; each participant group comprises one child with communication impairment, plus one parent, one teacher, one SLT, one teaching assistant and one typically developing partner child. The randomisation will occur at the level of the SLT because once an SLT has become familiar with E-PLAYS, it is possible that their approach to children with social communication difficulties may be influenced. Therefore, SLTs will receive immediate training if randomised to the intervention group and if allocated to the control group, will receive training after all study measures have been completed.

Participating children in the intervention arm will receive the E-PLAYS intervention while participating children in the control arm will receive treatment as usual. The trial will be pragmatic in nature with the interventions being delivered in the way that they would be delivered within the NHS. The effectiveness of E-PLAYS will not be addressed in this feasibility trial but left to a subsequent full-scale RCT, with the key outcomes of the present study relating to the feasibility of conducting such an RCT. Assessment of these feasibility outcomes will inform whether a full-scale trial is viable and inform its design and implementation.

### Setting

We will recruit SLTs and suitable children on their caseloads from within North East London NHS Foundation Trust (NELFT) Speech and Language Services.

### Participants

Participants will comprise the following in a ‘participant group’ comprising one child with social communication impairment (SCI) with associated relevant others:SLTs from NELFTParticipating children (ages 4–7 years old) with SCI as selected by SLTs ‘focal children’Teaching assistants trained to use E-PLAYS by participating SLTsTeachers who will complete pre-, post- and follow-up test measures relating to participating children‘Partner’ children; classmates for the focal children for the E-PLAYS intervention who will play the dyadic collaborative computer games that comprise E-PLAYS with them.Parents of the focal children who will complete post-test measures for health economics.

### Selection, recruitment and consenting of participants

The procedure for distribution of information sheets and consent forms for the different kinds of participants is described below. In all cases, potential participants will be given at least 48 h in which to make a decision.SLTs from NELFT

The research team will approach suitably employed paediatric SLTs, that is SLTs working with children aged 4- to 7-years-old attending mainstream (not special) schools. The SLTs will be invited to a presentation by the team, will have the opportunity to ask questions about the study and will be given information sheets and consent forms to take away to read. Consent forms can be returned by post, electronically or by hand to the research team. SLTs not responding within a week will be reminded and invited again by email once more only.(b)Participating children with social communication impairments (SCI) ‘focal children’.

SLTs will review their caseloads and identify suitable children using the Social Communication Behaviour Checklist devised by Adams et al. [40]. The checklist requires the SLT to decide on the applicability of each of the following five statements to a given child:The child has trouble understanding and interpreting the social context and friendship, e.g. social roles, emotionsThe child has trouble understanding and/or using non-verbal aspects of communication, e.g. facial expression, intonationThe child has trouble with aspects of conversation, e.g. beginning and ending, taking turns, giving relevant and sufficient informationThe child makes bizarre, tangential or inappropriate commentsThe child has difficulty using and understanding non-literal language

Children who are judged as having at least two of the five statements applying to them will be considered eligible for inclusion in the study provided they also meet the following additional criteria:Four- to seven-years-old at the time of the SLT’s assessment of eligibilityHave at least minimum levels of English (including any children with English as an additional language)Not suffering with a hearing, visual or physical impairment severely affecting speech production

Once eligibility is confirmed, the research team will provide schools with participant information sheets to send to parents, one written for parents and one written in simpler terms for the child to share with their parent, as well as a consent form for parents to sign.(c)Teaching assistants trained to use E-PLAYS by participating SLTs

Once the children with SCI have been selected by SLTs and consent has been received from parents, the teaching assistants who are supporting these children will be invited to take part in the study and will receive written information sheets and consent forms at school from the research team.(d)Teachers who will complete pre-, post- and follow-up test measures relating to participating children

Teachers of recruited children will also be invited to take part in the study and will receive written information sheets and consent forms at school from the research team.(e)‘Partner children’ for focal children for the E-PLAYS intervention

‘Partner children’ will be suggested by teachers and teaching assistants in consultation with the relevant SLT. These children will be typically developing children without language disorders in the same class as the focal children. E-PLAYS comprises a series of dyadic computer games, some of which are played with an adult and some with the partner child. The importance of the role that peers can play in interventions has been the subject of a recent systematic review by [41]). These authors concluded that the inclusion of peers was one of the most promising strategies for intervention and resulted in positive impacts on social communication. An important aspect of peer-mediated interventions concerns the peers chosen to interact with focal children. These peers can provide appropriate language models and also an opportunity for children with SCI to practice newly acquired skills. In general, it has been reported that teachers children who are popular, prosocial, and self-confident as peer partners for interventions [42]. Locke et al.’s longitudinal study [42] did not report any adverse outcomes for typically developing children as a result of participating in a peer-mediated intervention. An important feasibility question will concern recruitment of these children and willingness of parents to allow participation. Schools will send participant information sheets to parents of the peer partner children, one written for parents and one written in simpler terms for the child to share with their parent (as above for children with social communication impairment), as well as a consent form for parents to sign.(f)Parents of the children with SCI who will complete post-test measures for health economics.

Parents will be asked to consent to completion of these forms at the same time as they will be asked to provide consent on behalf of their children (b) above.

Whilst research assistants will pass on information sheets to participants via schools and request the return of consent forms, all participants will be given the option to contact the Chief Investigator in the event of additional questions. All participants will be free to withdraw at any time from the protocol treatment without giving reasons and without affecting their usual standard of care. The Chief Investigator will preserve the confidentiality of participants taking part in the study and is registered under the Data Protection Act.

### Randomisation and allocation process

Participating children with SCI will be cluster-randomised at the level of the SLTs. SLTs will be randomised 1:1 to receive either immediate briefing from the research team together with the manual on the E-PLAYS intervention or at to receive this at the end of the trial. Randomisation will take place after SLTs have consented to participate in the study, and have identified and recruited children on their caseloads to participate in the trial but before they receive briefing. Allocation will be via minimisation to ensure balance across the two groups based on the borough of the SLT (there are five boroughs within the district covered by NELFT, each served by a different SLT team) and number of children recruited (dichotomised around the median number of children recruited to form a two level factor). All SLTs will be randomised together as opposed to having a rolling recruitment/randomisation period. The minimisation will be implemented by the trial statistician at the York Trials Unit using MinimPy version 0.3. Once the allocations have been generated, they will be communicated to members of the research team responsible for training the SLTs, while ensuring that the outcome assessors (research assistants) remain blind to these allocations.

### Blinding

Parent- and teacher-completed measures cannot be blinded; however, measures collected by research assistants (RAs) will be blinded. Teachers and teaching assistants at the schools will be reminded not to reveal allocations to the research assistants at every visit. For the qualitative data collection (Fun Tool Kit, open-ended training questionnaires, observations and focus groups) in which blinding is not possible, research assistants will not collect data from the same schools in which they are collecting quantitative data in order to preserve blinding.

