#### (a) Speech and language therapists’ and teaching assistants’ views

Focus groups with the speech and language therapists and teaching assistants who delivered E-PLAYS will be conducted once delivery is complete, and their views sought on acceptability and ease of use.

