#### (c) Fidelity evaluation

(i)On-line recording of the number of intervention sessions completed for each child and their content and duration in minutes will be automatically logged by the E-PLAYS software. For the E-PLAYS computer game, each child will have their own unique login, which will record the number of sessions undertaken, the time that they lasted and which parts of the programme were completed.(ii)E-PLAYS sessions will be observed live by RAs to assess how faithfully teaching assistants actually use it in practice.(iii)We will also explore fidelity issues in the focus groups described above.

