### Analysis of outcome measures

A detailed analysis plan will be produced prior to the final analysis and will be reviewed by the independent trial steering committee. Analyses will follow intention to treat principles, with all data analysed as randomised. Analyses will be entirely descriptive with scores on the TPS, CCC-2, CELF-5 Recalling Sentences Subscale and Magformers® construction task presented unadjusted at each time point.

For the Magformers® construction task, video-recordings will be professionally transcribed and video-coding will comprise observation and categorisation of communicative (e.g. questions, directives, clarifications) and affective (e.g. positive and negative behaviours) items. The coding system is based on micro-analytic theory [52, 53] and was developed by the team specifically to analyse children’s collaborative interaction and has been shown in our studies to successfully detect changes in talk [29, 39, 54, 55]. The coding system incorporates elements from research into collaborative learning, conversation analysis and language impairment [29, 39, 53–60]. Video interaction will be coded by blinded RAs trained to fidelity by the Chief Investigator who has used this coding system extensively. RAs will train by watching and practice-coding training videos until they reach inter-rater reliability with these previously coded video-recordings. Areas of disagreement with the training videos will be discussed and explained by the Chief Investigator. Inter-rater reliability will further be tested between all RAs taking part in the study using a sample of 15% of all video-recordings.

The analysis of all measures will not be concerned with the effectiveness of the study intervention, but instead will seek to inform the feasibility objectives. In particular, this data will be used to characterise the groups at baseline, assess the proportion of analysable data at follow up and provide estimates of key population parameters, all of which will inform the design of a future full scale trial. The analysis of the health economic data will be principally concerned with the completeness and quality of this data. This will be reported together with a calculated estimate of the costs of running E-PLAYS within the NHS and schools and costs of a possible future full-scale RCT.

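### Assessor blinding is protected by school while allocation is by therapist, so a research assistant could keep to the rule and still assess or code children whose arm they can work out

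*Protocol article*

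**What the plan says.** All references are to the protocol article.

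- **Unit of allocation.** Randomisation and allocation process: "Participating children with SCI will be cluster-randomised at the level of the SLTs". The same section says that the outcome assessors, who are the RAs, are to stay blind to these allocations.
- **Unblinded work.** The Blinding section concerns the following: "For the qualitative data collection (Fun Tool Kit, open-ended training questionnaires, observations and focus groups) in which blinding is not possible". For this work its safeguard is that "research assistants will not collect data from the same schools in which they are collecting quantitative data in order to preserve blinding". The only other safeguard is a reminder to teachers and teaching assistants (TAs), at each visit, not to disclose the arm.
- **Who does it.** Process evaluation, Fidelity evaluation: "E-PLAYS sessions will be observed live by RAs to assess how faithfully teaching assistants actually use it in practice". RAs also run the Fun Toolkit.
- **SLT-level qualitative work.** Process evaluation (a): "Focus groups with the speech and language therapists and teaching assistants who delivered E-PLAYS will be conducted once delivery is complete". SLTs also complete a questionnaire shortly after receiving the instruction pack.
- **Blinded outcomes.** The Test of Pragmatic Skills (TPS), the CELF-5 Recalling Sentences subscale and the Magformers task are administered, and the Magformers recordings coded, by blinded RAs. Assessments are at baseline, 15–20 weeks and 35–40 weeks after randomisation.
- **Reliability sample.** Analysis of outcome measures: "Inter-rater reliability will further be tested between all RAs taking part in the study using a sample of 15% of all video-recordings".

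**The concern.** In a cluster trial, knowing the arm of one member of a cluster gives the arm of all of them. A rule meant to keep assessors blind therefore has to work at the level of the cluster. Here it works one level below, which leaves three gaps.

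1. **Same SLT, different school.** An RA who watches a session in one school learns that SLT's arm. The rule bars the RA from assessing children in that school, but not the same SLT's children elsewhere.
2. **SLT-level contacts.** A focus group or questionnaire with SLTs is not tied to one school, so a school rule does not clearly apply to it.
3. **Coding.** The rule is about collecting data. The article says that videos are coded by blinded RAs, yet has all RAs take part in the reliability check. Those RAs may include some who observed delivery, and nothing keeps recordings from clusters they know out of their sample. This gap remains even if every SLT serves one school.

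Observations and Fun Toolkit sessions take place during delivery, so they come before both follow-up assessments. At stake is whether TPS, CELF-5 and Magformers, the only outcomes described as blinded, can be presented as such, and whether a misplaced safeguard passes into the full trial that this study is meant to prepare.

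**Working it through.** The article gives no figure for this exposure, so there is none to reproduce. The sums below only gauge its possible size.

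**Inputs (Sample sizes section).** 35 children per arm; around 7 intervention SLTs and 19 TAs; 10 TAs observed live.

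**Ratios.** Children per SLT: 35/7 = 5.0. TAs per SLT: 19/7 = 2.7. Children per TA: 35/19 = 1.84. With 2.7 TAs and 5 children each, an SLT working in more than one school is likely, but the article does not say so.

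**Assumptions, none of them in the article.** The ten observed TAs are a random ten of 19; TAs are spread over SLTs as 3, 3, 3, 3, 3, 2, 2; different TAs are in different schools; RAs know which SLT each child belongs to; the observing RAs count as one person.

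**SLTs with at least one observed TA.** For an SLT with n TAs, the chance that none is observed is C(19−n, 10)/C(19, 10):

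- n = 3: 8008/92378 = 0.0867
- n = 2: 19448/92378 = 0.2105

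Expected number of SLTs reached = 5 × (1 − 0.0867) + 2 × (1 − 0.2105) = 4.57 + 1.58 = 6.1 of 7.

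**Unobserved TAs under a reached SLT.** Nine TAs are unobserved. Those under an SLT with no observed TA number 5 × 3 × 0.0867 + 2 × 2 × 0.2105 = 1.30 + 0.84 = 2.14. The rest are 9 − 2.14 = 6.9, and 6.86 × 35/19 = 12.6, about 13 children.

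**Sensitivity to the spread of TAs.** With 4, 4, 3, 3, 2, 2, 1 or 5, 4, 3, 3, 2, 1, 1 the SLTs reached are 5.9 and 5.6, and the unobserved TAs under them remain 6.9. If the observed TAs are chosen deliberately, the number can be anything from 0 to 9 TAs.

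**Sensitivity to the number of RAs.** Suppose R RAs are rostered at random. If j of an SLT's TAs are observed, the RA sent to one of its unobserved TAs' schools has seen at least one of the j with probability 1 − (1 − 1/R)^j. For R = 2:

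- n = 3: P(j=1) = 0.3715 and P(j=2) = 0.4180, giving 2 × 0.3715 × 0.5 + 1 × 0.4180 × 0.75 = 0.685 TAs per SLT
- n = 2: P(j=1) = 0.5263, giving 0.5263 × 0.5 = 0.263 TAs per SLT

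The total is 5 × 0.685 + 2 × 0.263 = 3.95 TAs, or 3.95 × 35/19 = about 7 children. The same formula gives about 5 children for R = 3 and 4 for R = 4.

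**What the count leaves out.** It covers only children whose own TA was not observed. Under the rule, an observed TA's school goes to a different RA. If that RA observed another TA of the same SLT, those children are exposed too. For R = 2, with P(j=3) = 0.1238 for n = 3 and P(j=2) = 0.2632 for n = 2, this adds 5 × (2 × 0.4180 × 0.5 + 3 × 0.1238 × 0.75) + 2 × (2 × 0.2632 × 0.5) = 4.0 TAs, about 7 further children. So 13 is a ceiling for the group counted, not for every possible roster.

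**The case against.** The strongest reply is that unblinding needs links that the article does not supply. It does not say that an SLT serves several schools, that an RA testing a child knows the child's SLT, or how many RAs there are. Testing takes place in schools, and SLTs have no stated part in it. This stands, and it makes the exposure conditional. It does not remove the gap: nothing in the article hides SLT identity from RAs, and nothing separates RAs by SLT.

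Second, the reliability sample is an agreement check. The article does not say that the second codes replace the outcome codes, so a coder who knows the arm would mainly affect the reliability estimate. This also stands.

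Third, the analyses are wholly descriptive and effectiveness is explicitly left to a later trial. That limits the severity, but it does not make a rule set at the wrong level harmless in a study whose purpose is to develop the full trial's protocol.

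A reader might also infer that SLT focus groups are bound to unblind assessors before the last follow-up, revealing the arm of 20 to 25 children (four or five SLTs at 5 children each). The text does not support this. Completion of delivery sets an earliest date for the groups and no latest one, the section describing them names no facilitator, and the figure would require that facilitator to go on to assess those children.

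**Conclusion.** The mismatch is on the face of the text: separation is by school, allocation is by SLT, and no other section closes the gap. An RA can therefore follow the rule fully and still assess or code children whose arm they are able to infer. This rests on two unstated conditions: that SLTs cover more than one school, which is likely, and that RAs can link children to SLTs, which is open. The coding gap needs neither condition when the recordings come from the school that the RA observed.

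Under the listed assumptions, about 13 of the 35 intervention children are exposed among those whose own TA was not observed; in that group the number falls to about 7, 5 or 4 with two, three or four randomly rostered RAs.

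Two stronger readings should be resisted. One is that following the rule does unblind the assessments; the article shows only that it can. The other is that the trial will report blinding as workable; blinding is not among its stated objectives or feasibility outcomes, and no such report is planned. The harm is to the credibility of the TPS, CELF-5 and Magformers data as blinded data and to the procedure handed on. Severity: moderate.

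**What to change.** - Define the separation by SLT cluster: an RA who has done qualitative work with an SLT, or with any TA or school under that SLT, does not afterwards test, record or code any of that SLT's children.
- Have an unblinded team member draw up the roster and keep SLT identity from assessors. Otherwise, rostering by SLT could itself give assessors the link that unblinds them.
- Hold SLT focus groups after the 35–40-week assessments, or have them run by someone who will not assess or code those SLTs' children. Using the team members who trained the SLTs would preserve blinding, but they would be asking for views on their own briefing and manual.
- Draw each RA's reliability videos only from SLTs to which that RA is still blind.
- Record any unmasking at each blinded visit.

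The cost is less flexible RA scheduling and one extra form field. Whether more staff are needed cannot be judged, because the number of RAs is not given. Trial status reports that delivery is already under way, so some observations may have been done. The change can still govern focus groups, remaining assessments and coding, and the full trial's protocol.
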